#### Inclusion criteria check

2.2.5

Inclusion criteria will be checked by Occupational Safety and Health Technician prior to OM appointment.

#### Demographics and disease history

2.2.6

At baseline, demographics and disease history will be recorded on paper by the Occupational Safety and Health Technician during OM appointments. The study coordinator will later collect these records, assign a participant number to replace the SNS number in the eCRF, and generate a key pair to link the SNS number with the participant number. At T0 and T12, smoking habits and disease history will also be initially recorded on paper by the hospital medical doctor, and the same process of replacing the SNS number with a participant number and recording the key pair will be followed for entry into the eCRF.

#### Diet questionnaire

2.2.7

Diet questions from Life's Essential 8 questionnaire (14) will be mandatory for participants under 40 years old. These data will be recorded by Occupational Safety and Health Technician before the OM appointment.

#### Usual medication

2.2.8

At baseline, usual medication will be recorded on paper by the Occupational Safety and Health Technician during OM appointments, with the data later entered into the eCRF. At T0 and T12, usual medication will be recorded on paper by the hospital medical doctor, following the same process for entry into the eCRF.

#### Prescribed medication

2.2.9

At T0 and T12, any newly prescribed medication will be recorded on paper by the hospital medical doctor after the clinical evaluation, with the data later entered into the eCRF.

#### Clinical evaluation

2.2.10

At baseline, clinical evaluation will be recorded on paper by the Occupational Safety and Health Technician during OM appointments, with the data later entered into the eCRF. At T0 and T12, clinical evaluation will be recorded by the hospital medical doctor and entered into the eCRF.

#### Laboratory testing

2.2.11

At baseline, laboratory testing results will be recorded on paper by the Occupational Safety and Health Technician before OM appointments, with the data later entered into the eCRF by the study coordinator. At T0 and T12, laboratory results will be recorded by the hospital medical doctor and later entered into the eCRF by the study coordinator.

#### Destination

2.2.12

These variables are related to the referral given to the participant after the clinical evaluation. At the baseline, the OM doctor indicates whether advice was given, referred to Family Medicine, or to a hospital; at T12, the hospital medical doctor indicates whether participant was discharged or continue with hospital follow-up.

#### Medication adherence questionnaire

2.2.13

At T12, medication adherence questions from the adapted Simplified Medication Adherence Questionnaire (SMAQ) will be answered on paper and later entered into the eCRF by the study coordinator. The adapted SMAQ was selected because it is a brief, easily administered instrument suitable for routine clinical practice and implementation studies involving patients receiving multiple long-term medications. Although originally validated in renal transplant recipients, it has been used as a pragmatic measure of medication adherence across chronic disease settings (15, 16).

### Data management and analysis

2.3

An eCRF will be developed by the CRO for data collection, aligned with study's specific objectives and researchers’ preferences, and will be hosted by ULSEDV on the institution's approved RedCAP system. During OM and hospital appointments, data will be initially recorded on paper, including the SNS number and visit date, and stored alongside other clinical records under the same security measures. The study coordinator will periodically collect these paper records from the study sites, assign a participant number to replace the SNS number in the electronic records and generate a key pair to link the SNS number with the participant number. The coordinator will then enter the collected data into the eCRF and ensure the accuracy of data. The key pair and original paper source documents will be stored at ULSEDV in compliance with institutional regulations. The date of each visit will also be recorded.

The sponsor, NVS, and the designated CRO, MTG Research & Development Lab, will have oversight of the data management process but will not directly handle any patient-identifiable information. Primary statistical analyses will be conducted by the CRO and ULSEDV-affiliated investigators independently of Novartis Portugal. Novartis Portugal will have no access to patient-level data, will not perform or direct the statistical analyses, and will not have authority over the interpretation of results or the decision to publish, consistent with ICMJE and GPP recommendations on sponsor independence.

#### Statistical methods

2.3.1

To address the multifaceted endpoints of this study (Table 3), a combination of statistical techniques will be employed. Descriptive statistics will be calculated to assess various CV risk factors. Continuous variables will be summarized using n, mean, median, standard deviation, minimum, maximum and 25th and 75th percentiles. Categorical variables will be summarized using frequency counts and percentages. Missing data will be reported using frequency counts and percentages and assessed for pattern and extent; where data are judged to be missing at random, multiple imputation will be used as the primary approach. Outliers will be identified using standard distributional criteria, and treated in consideration of their impact on the analysis.

**Table 3 T3:** Cardiogap + endpoints.

Endpoint Description
1. Proportion (%) of patients who meet the follow-up criteria for CV risk hospital consultation identified in OM consultation: Descriptive statistics will be used to calculate the percentage of patients who meet the follow-up criteria for CV risk hospital consultation over all patients attending OM consultations.
2. Proportion (%) of High CV risk individuals identified in OM consultation: Descriptive statistics will be used to calculate the percentage of High CV patients over all patients attending OM consultations.
3. Proportion (%) of Very High CV risk individuals identified in OM consultation: Descriptive statistics will be used to calculate the percentage of Very High CV patients over all patients attending OM consultations.
4. Proportion (%) of patients referred to Hospital CV Risk Consultation, overall and stratified by risk category: Descriptive statistics will be used to calculate the percentage of patients referred to Hospital CV Risk Consultation, reported (a) over allpatients meeting follow-up criteria, (b) over High CV risk patients only, and (c) over Very High CV risk patients only, identified in OM consultation.
5. Proportion (%) of Hospital CV Risk Consultation Participation after Referral by OM: Descriptive statistics will be used to calculate the percentage of individuals referred from OM consultations who participate in hospital CV risk consultations over all patients referred to hospital consultations.
6. Level of Adherence to Medication Prescribed in the Hospital CV Risk Consultation: Descriptive statistics will assess the adherence levels, measured by SMAQ among patients prescribed medications in the hospital CV risk consultations.
7. Proportion of Patients Who Attended Smoking Cessation Consultation: Descriptive statistics will determine the proportion of patients attending smoking cessation consultations over patients who were referred and participated in hospital CV risk consultation.
8. Change in distribution from Baseline in Various CV Risk Factors after 12 Months: Appropriate statistical methods will be used to calculate the distribution change from baseline (first hospital consultation) for the following CV risk factors after the use of this simplified referral process.
a. LDL-C
b. Blood pressure (SBP and DBP)
c. Moderate or severe chronic kidney disease
d. Smoking status
e. HbA1c
f. BMI
Statistical methods for this endpoint are specified in Section 2.3.1.
9. Distribution of Lipoprotein (a) at the first hospital consult: Descriptive statistics will assess the distribution of Lipoprotein (a) at the first hospital consult.
10. Prevalence of CV Risk Factors in the industrial/manufacturing in São João da Madeira: Appropriate statistical methods will be used to estimate the prevalence of CV risk factors within the industrial/manufacturing companies, including the levels of Lipoprotein (a) among very high CV risk individuals.
11. Proportion (%) of Identified Patients Referenced to GP Consultation: Descriptive statistics will be used to calculate the percentage of patients referred to GP consultations.

For the change in CV risk factors from baseline/T0 to T12, repeated continuous measures will be analyzed using linear mixed-effects models (or generalized estimating equations, as appropriate to the outcome distribution) with a random intercept per participant to account for within-subject correlation across the baseline, T0 and T12 assessments. Binary or categorical repeated measures will be analyzed using generalized estimating equations with a logit link. Models will be adjusted *a priori* for age, sex, baseline CV risk category, and baseline value of the outcome variable; additional covariates identified as clinically relevant confounders may be added in sensitivity analyses.

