dieta_doces_semana	How many servings of commercial sweets, candy bars, pastries, cookies, or cakes do you consume per week?	Baseline
dieta_bebidas_acucaradas_semana	How many servings of sugar-sweetened beverages do you drink per week?	Baseline
Usual Medication		
anti_dislipidemico	Anti-dyslipidemic	Baseline, T0, T12
anti_hta	Anti-hypertensive	Baseline, T0, T12
anti_agregantes	Anti-platelet	Baseline, T0, T12
farmaco_sem_medicacao	Without Usual Medication	T0, T12
farmaco_mh_dci	Drug (Previous Usual Medication) - International Nonproprietary Name (INN)	T0, T12
farmaco_mh_dose	Drug (Previous Usual Medication) - Dose	T0, T12
outro_farmaco	Insert another drug	T0, T12
Prescribed Medication		
intervencao	Was a new drug prescribed as a result of this assessment?	T0, T12
farmaco_intervencao_dci	Newly Prescribed Drug - International Nonproprietary Name (INN)	T0, T12
farmaco_intervencao_dose	Newly Prescribed Drug - Dose	T0, T12
outro_farmaco_intervencao	Insert another drug?	T0,T12
Clinical Evaluation		
ta_sist	Systolic Blood Pressure (mmHg)	Baseline, T0, T12
ta_diast	Diastolic Blood Pressure (mmHg)	Baseline, T0, T12
fc	Heart Rate (bpm)	Baseline, T0, T12
peso	Weight (kg)	Baseline, T0, T12
altura	Height (cm)	Baseline, T0, T12
Laboratory testing		
data_avaliacao_analitica	Date of Analytical Assessment	Baseline, T0, T12
colesterol_total	Total Cholesterol (mg/dL)	Baseline, T0, T12
ldl_c	LDL-C (mg/dL)	Baseline, T0, T12
hdl_c	HDL-C (mg/dL)	Baseline, T0, T12
triglicerideos	Triglycerides (mg/dL)	Baseline, T0, T12
hba1c	HbA1c (%)	Baseline, T0, T12
creatinina	Creatinine (mg/dL)	Baseline, T0, T12
egfr	Estimated Glomerular Filtration Rate (mL/min/1.73m^2^)	Baseline, T0, T12
ureia	Urea (mg/dL)	Baseline
lp_a	Lipoprotein (a)	T0
apo_a	Apolipoprotein A	T0, T12
apo_b	Apolipoprotein B	T0, T12
Destination		
destino_consulta_mo	Destination of the Participant	Baseline
destino_final_hospitalar	Destination After 12 Months of Hospital Follow-Up	T12
Medication adherence questionnaire		
qat_1_toma_hora	Do you always take your medication at the appropriate time?	T12
qat_2_sentir_mal	When you feel bad, have you ever discontinued taking your medication?	T12
qat_3_esquecer	Have you ever forgotten to take your medication?	T12
qat_4_esquecer_fds	Have you ever forgotten to take your medication during the weekend?	T12
qat_5_falha_semana	In the last week, how many times did you failed to take your prescribed dose?	T12

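### Endpoint 6 is titled as adherence to the hospital-prescribed drugs, but its only measure, the SMAQ at T12, asks about the patient's medication in general

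*Protocol article*

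**What the plan says.** Table 3 of the protocol article titles endpoint 6 "Level of Adherence to Medication Prescribed in the Hospital CV Risk Consultation" and specifies: "Descriptive statistics will assess the adherence levels, measured by SMAQ among patients prescribed medications in the hospital CV risk consultations". No other measure is named, and no other endpoint concerns adherence.

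Table 2 prints the six items, all collected at T12 only. The first four are "Do you always take your medication at the appropriate time", "When you feel bad, have you ever discontinued taking your medication", "Have you ever forgotten to take your medication" and "Have you ever forgotten to take your medication during the weekend". The fifth asks how often in the last week the prescribed dose was missed. The sixth asks for the number of whole days without medication since the last visit.

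Section 2.2.13 says that the adapted SMAQ was chosen partly because it suits patients on several long-term drugs.

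Table 2 also keeps two separate drug lists at T0 and T12, each with name and dose. One is headed "Drug (Previous Usual Medication) - International Nonproprietary Name (INN", the other "Newly Prescribed Drug - International Nonproprietary Name (INN". A further field marks patients without usual medication. Broad drug classes (lipid-lowering, antihypertensive, antiplatelet) are recorded from baseline.

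Secondary objective 3 (section 2.1.2) judges the referral process partly by therapeutic adherence. Section 2.2 gives estimating adherence to drug therapy as a purpose of the 12-month follow-up phase.

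**The concern.** The title promises adherence to a specific set of drugs, those prescribed at the hospital. The instrument asks about whatever the patient regards as their medication. The two agree when the hospital drug is the patient's only drug. They can differ when the patient also takes older tablets, a situation that the protocol expects, since it chose the instrument for patients on several drugs and records usual drugs separately from new ones.

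Secondary objective 3 is at stake. Endpoint 6 is the only adherence result the study will produce. As titled, it would be read as showing whether patients kept taking what the hospital consultation started. Endpoint 8 reports LDL-C and blood pressure over the same 12 months, and readers will naturally set the two side by side. A score that mixes old and new drugs does not tell them whether the hospital drug was still being taken.

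**Working it through.** **1. The plan's own figure.** The article gives no figure for endpoint 6. Its one precision figure (section 2.2.2) reproduces: 1.96 × √(0.15 × 0.85 / 1000) = 0.0221, the stated 2.2%. It concerns prevalence among 1000 workers and says nothing about adherence. The same section expects 150 hospital appointments (0.15 × 1000 = 150). On that expectation, 150 is a ceiling for endpoint 6, because its denominator is only those prescribed a drug and assessed at T12.

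**2. Items against title.**

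| Item | Refers to | Time window | Names the hospital drug? |
|---|---|---|---|
| 1 to 4 | medication in general | none stated | no |
| 5 | prescribed dose | last week | no; drug and prescriber unspecified |
| 6 | medication in general | since the last visit | no; fixes the period, not the drug |

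Five items use the general word and one the prescribed dose. Items 1 to 4 have no window, so for a patient already on treatment they can reach back before T0.

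**3. Both directions of error.** Consider patients prescribed a drug at T0 who also take older drugs.
- One has stopped the T0 drug, takes the older tablets faithfully and reads the questions as being about current tablets. All six answers can be truthful and adherent.
- One takes the T0 drug faithfully but sometimes forgets an older tablet. The answers to items 1, 3 and 4, and possibly 5, point to non-adherence.

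A patient whose only drug was the hospital drug, and who answers about it, would reveal a stop through items 5 and 6.

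**4. Illustration; every input is an assumption.** Let *a* be true adherence to the hospital drug, *u* the share of patients non-adherent to it who score adherent through other drugs, and *v* the share adherent to it who score non-adherent through other drugs.

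Measured adherence = a(1 − v) + (1 − a)u, so net error = (1 − a)u − a·v.

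Upward part alone, 100 × (1 − a)u, in percentage points:

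| a | u = 0.1 | u = 0.3 | u = 0.5 |
|---|---|---|---|
| 0.5 | 5 | 15 | 25 |
| 0.7 | 3 | 9 | 15 |
| 0.9 | 1 | 3 | 5 |

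With the downward part, at a = 0.7 and u = 0.3:
- v = 0.1: 0.09 − 0.07 = +2 points.
- v = 0.3: 0.09 − 0.21 = −12 points.

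The sign changes with *v*, and the documents give none of the three inputs.

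**5. Scale.** The 95% half-width at a proportion of 0.5 is 1.96 × √(0.25/150) = 8.0 points with 150 patients, and 1.96 × √(0.25/100) = 9.8 points with 100 (an assumed number). Misclassification could therefore be smaller or larger than sampling error.

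**6. What the collected fields allow.** Names of drugs newly prescribed at T0 can be matched with names on the usual-medication list at T12. That shows whether a T0 drug is still listed, has gone, or has been replaced by another of its class. No listed field records why it went. No endpoint in Table 3 uses the match.

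**The case against.** The strongest reply is that Table 2 lists database labels, not the administered form. The adapted questionnaire is answered on paper, and an instruction to answer about the hospital drugs could sit there or in the full protocol. That is possible and limits confidence, but the article states no such instruction, and the items as printed do not supply one.

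Second, item 6 is anchored to the last visit, and T0 is the only earlier hospital assessment listed. With item 5, it would catch many patients who stopped their only drug. The pathway also aims at workers whom primary-care screening often misses, so prior treatment may be uncommon. Both points stand. They narrow the affected group without removing it.

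Third, the endpoint is descriptive and secondary, and risk-factor change is declared exploratory. This also stands and limits the consequence.

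A reader might go further and infer any of the following, which the documents do not support:
- *The endpoint overstates adherence by a known amount.* The error can run either way, and no input is given.
- *Patients who stopped everything drop out of the endpoint.* They can still answer items 5 and 6. No exclusion is stated, and section 2.3.1 says missing data will be counted and assessed.
- *Stopping and switching go unrecorded.* Both can be derived from the two drug lists; only the reason is absent.
- *A flat LDL-C result therefore cannot be interpreted at all.* No comparator is described, so causal attribution was not on offer, and the drug lists still allow non-persistence to be examined.

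**Conclusion.** The point holds in a limited form. The title of endpoint 6 and its sole measure refer to different sets of drugs, and nothing in the article reconciles them. The score can misclassify adherence to the hospital drug in patients who take other long-term drugs, including by counting as adherent someone who stopped it. The size and net direction are unknown; the figures above only show what assumed inputs would imply. The conclusion rests on two assumptions: that some analysed patients take other long-term drugs, which section 2.2.13 implies, and that the paper form carries no instruction tying the answers to the T0 prescription. It is worth correcting because this is the only adherence endpoint under secondary objective 3. It does not threaten the primary objective.

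**What to change.** 1. Make the title and measure agree. Either report the SMAQ result as overall medication adherence at T12, or instruct patients on the form to answer about the drugs prescribed at T0.
2. Confirm that the T12 usual-medication field records drugs actually being taken, including those started at T0. Its label refers to previous usual medication and the hospital doctor completes it, so it might list drugs prescribed rather than taken. The next step depends on this.
3. Add a descriptive persistence measure: among patients with a drug newly prescribed at T0, the proportion whose T12 usual-medication list still contains that drug name. Report same-class switches and patients without usual medication as separate categories, not as failures. Present it beside the SMAQ result, since persistence and adherence are different quantities.
4. Optionally, add one T12 item for each T0 drug no longer taken: stopped or switched by a doctor, or stopped by the patient. Without it, doctor-directed stops cannot be told apart from non-persistence.

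The cost is a wording change, a small matching analysis of fields already collected, and at most one extra item at a visit already planned.

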**Figure 1 F1:**
[figure not shown]
Overview of patient participation and data collection. OM: Occupational Medicine; CV: cardiovascular; T0: first hospital consultation; T12: 12-month hospital consultation; a) CV risk consultation and/or Smoking cessation consultation, when applicable; b) Risk prediction algorithms: SCORE2 for patients aged 40 years or more with HDL available; SCORE for patients aged 40 years or more without HDL available; c) Risk prediction algorithms: SCORE2 for patients aged 40 years or more. The enrollment phase includes the OM consultations occurring in the identified companies. The follow-up phase includes the hospital appointments occurring in ULSEDV.

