##### Exclusion criteria

2.2.1.1

Only workers unwilling or unable to complete the assessments will be excluded.

Criteria of follow-up match the criteria for referral to a cardiovascular risk appointment by the Occupational Health physician. These criteria will be based on the Cardiovascular Prevention recommendations from 2021 of the European Society of Cardiology (ESC) and are as described in Table 1, regardless of whether there is a previous history of atherosclerotic disease. The combined use of the SCORE2 and SCORE algorithms reflects data availability in the OM setting: in the case of unavailability of HDL-cholesterol in the OM setting, the legacy SCORE algorithm is used as a pragmatic fallback, consistent with the flexibility allowed under the 2021 ESC guidelines (4, 11, 12).

**Table 1 T1:** Criteria for referral to a cardiovascular risk appointment by the occupational health physician, based on the cardiovascular prevention recommendations from 2021 of the European Society of Cardiology (ESC).

*Markedly elevated single risk factor*
• Total cholesterol >310 mg/dL or LDL cholesterol >190 mg/dL
• Blood pressure >180/110 mmHg
• Moderate or severe chronic kidney disease, defined as eGFR <60 mL/min/1.73 m^2^ (CKD-EPI 2021 creatinine equation)

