#### Data collection

2.2.4

Participants will be assessed in three time points:
at baseline, at their working company by Occupational Safety and Health Technician and by OM doctorat T0, at hospital centre by a medical doctor, for participants referred by the OM doctor based on their CV-risk levelat T12, at hospital centre by a medical doctor, 12 months after T0.Study variables to be used in this study, and related definitions, are described in the following subsections. Table 2 shows the set of data that will be collected and variable features. The main study variables concern demographics, habits, laboratory testing, comorbidities, medications and destination are listed below in more detail.

**Table 2 T2:** Data collection – variables and corresponding features.

Variable	Label	Evaluation period
Inclusion Criteria Check		
consentimento_informado	Signed informed consent	Baseline
avaliacao_possivel	Participant willing and able to complete the assessments	Baseline
Demographics and disease history		
ano_de_nascimento	Birth year	Baseline
sexo	Sex	Baseline
tabagismo_status	Smoking status	Baseline, T0, T12
dieta	Enter Diet Data?^a^	Baseline
sono	On average, how many hours of sleep do you get in a 24-hour period?^b^	Baseline
exercicio_fisico	How many minutes of moderate (or greater) intensity activity per week?^b^	Baseline
drc_moderada_grave	Presence of Moderate or Severe Chronic Kidney Disease	Baseline, T0, T12
dm	Presence of Diabetes Mellitus	Baseline, T0, T12
historia_evento_cv	History of Cardiovascular Event	Baseline, T0, T12
especificacao_eventos_cv	Specification of Cardiovascular Events	Baseline, T0, T12
outros_antecedentes	Other Pathological History	Baseline, T0, T12
Diet Questionnaire		
dieta_porcoes_vegetais_semana	How many servings of vegetables do you consume per week?	Baseline
dieta_porcoes_carne_vermelha_semana	Servings of Red Meat per Week	Baseline
dieta_porcoes_manteiga_creme_semana	How many servings of butter or cream do you consume per week?	Baseline
dieta_porcoes_graos_integrais_dia	How many servings of whole grains do you consume per day?	Baseline
dieta_consumo_fastfood_semana	Times Consuming Fast Food Meals per Week	Baseline
por_es_de_frutas_por_semana	How many servings of fruit do you consume per week?	Baseline
dieta_peixe_semana	How many servings of fish or shellfish/seafood do you consume per week?	Baseline
dieta_feijoes_semana	How many servings of beans do you consume per week?	Baseline

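### Endpoint 7 divides smoking-cessation attendance by all hospital attendees, not by smokers, so it mixes smoking prevalence with uptake

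*Protocol article*

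**What the plan says.** Table 3 of the protocol article (Section 2.3.1) defines endpoint 7 descriptively, as the "proportion of patients attending smoking cessation consultations over patients who were referred and participated in hospital CV risk consultation". The natural reading is that the referral meant is the one from Occupational Medicine (OM) to the CV risk consultation, so the denominator is everyone who attended that consultation.

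The Figure 1 legend describes the hospital step as "CV risk consultation and/or Smoking cessation consultation, when applicable". Table 1 sets the referral criteria: a markedly raised single factor (for instance "Total cholesterol >310 mg/dL or LDL cholesterol >190 mg/dL"), or a SCORE2 or SCORE level. Smoking is not a listed criterion.

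On data, Section 2.2.4 states "Table 2 shows the set of data that will be collected and variable features". The only smoking variable in that table is "Smoking status Baseline, T0, T12". Section 2.2.12 describes two destination fields. At baseline, "the OM doctor indicates whether advice was given, referred to Family Medicine, or to a hospital"; and "at T12, the hospital medical doctor indicates whether participant was discharged or continue with hospital follow-up". Neither has a smoking-cessation category as described.

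**The concern.** A cessation consultation is meant for people who smoke. With all CV risk attendees in the denominator, each non-smoker enters as a patient who did not attend a service that does not apply to them. The result then moves with the smoking prevalence of the attendees even when uptake among smokers is constant.

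Neighbouring endpoints in Table 3 match the denominator to the population concerned. Endpoint 6 is confined to patients who were prescribed medication, and endpoint 4 is reported over three explicit risk groups. Endpoint 7 has no such restriction.

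At stake is what a reader can learn about the cessation arm of the pathway. The pilot is meant to inform a later evaluation, and a low value could mean few smokers or poor uptake, with nothing in the endpoint to separate the two.

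**Working it through.** **The plan's own figures.** The article states no expected value or precision for endpoint 7. Its only precision statement (Section 2.2.2) is a 2.2% margin for 15% prevalence with 1000 people. It reproduces: 1.96 × √(0.15 × 0.85 / 1000) = 2.21%. The expected number of CV risk appointments also reproduces: 0.15 × 1000 = 150. I use 150 as the expected endpoint 7 denominator, which supposes that all those referred attend.

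**Formula.** Let s be the share of current smokers among CV risk attendees and u the share of those smokers who attend cessation. If only smokers attend, then

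endpoint 7 = s × u, which is at most s.

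The article gives neither s nor u. All values below are assumptions chosen to show the range.

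**Same uptake, different smoker share (u = 60%).**

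- s = 25%: 0.25 × 0.60 = 15%
- s = 35%: 0.35 × 0.60 = 21%
- s = 50%: 0.50 × 0.60 = 30%

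The ratio of uptake to the reported figure is 1/s: 4, 2.9 and 2 respectively.

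**Same reported figure, different uptake.** If endpoint 7 came out at 15%, the implied uptake is 0.15 / s:

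| Smoker share s | Implied uptake |
|---|---|
| 20% | 75% |
| 30% | 50% |
| 40% | 37.5% |
| 50% | 30% |
| 60% | 25% |

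**With a smoker denominator.** Take u = 50% and 150 attendees. The smoker-based figure is 50% whatever s is, while the present definition gives s × 0.5. The 95% half-width is 1.96 × √(0.25 / number of smokers):

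| s | Smokers | Present endpoint 7 | Smoker-based figure | Half-width (points) |
|---|---|---|---|---|
| 20% | 30 | 10% | 50% | 18 |
| 30% | 45 | 15% | 50% | 15 |
| 40% | 60 | 20% | 50% | 13 |
| 50% | 75 | 25% | 50% | 11 |
| 60% | 90 | 30% | 50% | 10 |

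The smoker-based figure rests on fewer patients and will be imprecise, but it estimates uptake.

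**Data source.** Comparing Table 3 with Table 2: the smoker denominator can be formed from smoking status at T0. The numerator has no listed variable. Destination is recorded at baseline and T12 only, and neither field mentions cessation.

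**The case against.** The strongest reply is that endpoint 7 is a legitimate description of service use. It is titled as a proportion of patients who attended and does not claim to measure uptake among smokers, and no objective in Section 2.1.2 mentions cessation uptake. Smoking status is collected, so the smoker share can be reported beside it. This stands in part: the endpoint is well defined, and calling it uninterpretable would go too far. It remains a weak choice, because the more informative denominator is already in the planned data.

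A reader might also infer from Table 2 that the endpoint cannot be computed. The article does not show that. Section 2.2.4 also uses softer wording: "The main study variables concern demographics, habits, laboratory testing, comorbidities, medications and destination are listed below in more detail". Section 2.3 says that visit dates will be recorded, although Table 2 lists none, so the table is not demonstrably exhaustive. The full eCRF is not shown, and attendance might be taken from hospital appointment records. What stands is that the article names no source for the numerator.

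Finally, a reader might infer from the Figure 1 legend that someone could attend cessation without a CV risk consultation and so be in the numerator but not the denominator. The legend note belongs to a figure that is not available here, and the ordinary reading of endpoint 7 counts the numerator within the attendees. That inference is not supported.

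The multiples of 2 to 4 shown above are simply the inverse of the assumed smoker share, and they measure an understatement only if uptake among smokers is what the endpoint is meant to convey.

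**Conclusion.** The concern holds in a limited form. As defined, endpoint 7 is the product of smoking prevalence among attendees and uptake among smokers, and it is capped at the smoker share. The structure follows from the stated denominator and the referral criteria, on the assumption that only smokers attend cessation. The size depends on smoker share and uptake, which the article does not give, so the figures are illustrations. The missing numerator variable is an accompanying point about naming a source, not proof that the data will be unavailable. The matter is minor: one descriptive endpoint of eleven is affected, and no test, sample size or primary objective depends on it.

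**What to change.** Reword endpoint 7 as the proportion attending a smoking-cessation consultation among patients who attended the CV risk consultation and were current smokers at T0, with the numerator counted in that same group. Give numerator, denominator and a confidence interval. Keep the crude proportion over all attendees as a secondary description if wanted, with the smoker share beside it.

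In Table 2, name the source for cessation attendance (for example hospital appointment records) or add a dated yes/no field. If a denominator of those referred to cessation is also wanted, add a matching field for referral, since no listed variable identifies them.

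The new denominator needs no extra data collection. The rest costs one sentence naming the source, or one to two eCRF fields.
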